## Analysis plan

We will use descriptive statistics, mean and standard deviation for continuous variables and frequency and percent for categorical variables, to summarize participant characteristics and study outcomes. To determine feasibility of recruitment, we will calculate the time to recruit 1500 participants and the cost per study completer. We will calculate percent agreement and kappa coefficients with associated 95% confidence interval to determine validity of self-reported diagnoses. We will estimate the cross-sectional association of physical activity, pain, and physical function using linear regression adjusted for potential confounders.

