### Participants

Individuals will be recruited using Meta advertisements primarily through Facebook, the Arthritis Foundation mailing list, and via the ResearchMatch participant database. ResearchMatch is a national health volunteer registry that was created by several academic institutions and supported by the U.S. National Institutes of Health as part of the Clinical Translational Science Award (CTSA) program. ResearchMatch includes volunteers who have consented to be contacted by researchers about health studies for which they may be eligible. Review and approval for this study and all procedures was obtained from University of Delaware Institutional Review Board. Participants will be included if they are at least 18 years old, live in the United States, and report having a diagnosis of a rheumatic disease provided by a physician. Participants self-report diagnoses of OA, gout, fibromyalgia, RA, psoriatic arthritis (PsA), lupus, or ‘other’ rheumatic disease. Additionally, participants must have internet access, a working email address, feel comfortable answering questions in English, and be willing to have a virtual call to verify their identity. Participants will be excluded if they fail to meet any of the inclusion criteria, have been previously enrolled, or fail the identity verification check.

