### Disease Specific Information

Participants will self-report which rheumatic diseases they have been diagnosed with by a physician and the date of diagnosis for each. Participants will select from a list of OA, gout, fibromyalgia, RA, PsA, Lupus, or Other. If other is selected, participants are able to write in any other rheumatic disease they are diagnosed with. Participants will also be able to select multiple diagnoses. If the participant reports being diagnosed with osteoarthritis, they will be asked to report which joints were affected. National Institute for Health and Care Excellence (NICE) criteria for knee OA (≥ 45 years old, activity-related knee pain, and morning stiffness lasting < 30 minutes)^26^ will be assessed in all participants who report OA and specified the knee joint being affected. NICE Criteria have been shown to be sensitive and specific in detecting symptomatic knee OA. Participants will also be asked about previous joint injuries, joint surgeries, and past and current strategies used to manage their disease related symptoms, including options such as physical therapy, diet, corticosteroid injections, immunosuppressants, nonsteroidal anti-inflammatory medications, etc. The use of glucagon-like peptide-1 (GLP-1) agonists will also be assessed.^27,28^

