### Diagnosis Verification

Self-reported diagnoses will be verified via physician report or electronic medical record (EMR). Participants will specify whether they will provide EMR verification of their diagnoses or if they would prefer the research team to contact their physician for verification. Participants will then either upload a screenshot or scanned document from his/her EMR where their diagnosis is specified, or their physician will complete a provided diagnosis form template. In any instances where the specified diagnosis is unclear, the research team will adjudicate to determine whether the diagnosis can be confirmed.

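### Per-disease kappa cannot measure validity where a participant-chosen record page verifies only the claimed diagnosis; the confirmed proportion should be the validity measure

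*Protocol article*

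**What the plan says.** Validating patient-reported diagnoses is one of three aims in the protocol article (abstract, Objective; Introduction). Four places bear on how it is done.

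- **Participants.** To enter, a person must "report having a diagnosis of a rheumatic disease provided by a physician". Everyone enrolled therefore claims at least one disease.
- **Disease Specific Information.** "Participants will select from a list of OA, gout, fibromyalgia, RA, PsA, Lupus, or Other", and "Participants will also be able to select multiple diagnoses". That makes seven categories, which are not mutually exclusive.
- **Diagnosis Verification** (under Secondary Outcomes). "Self-reported diagnoses will be verified via physician report or electronic medical record (EMR"). The participant chooses the route. On one, they "upload a screenshot or scanned document from his/her EMR where their diagnosis is specified"; on the other, "their physician will complete a provided diagnosis form template". In unclear cases, "the research team will adjudicate to determine whether the diagnosis can be confirmed".
- **Analysis plan.** "We will calculate percent agreement and kappa coefficients with associated 95% confidence interval to determine validity of self-reported diagnoses".

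The article does not say that diseases a participant left unselected are looked for in the record. It does not define the table behind kappa, and it does not describe the content of the physician form.

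**The concern.** Kappa for a given disease compares two ratings, self-report and record, each of which must be able to be yes or no. It needs the record status of people who did not claim the disease as well as of those who did. The verification step, as described, yields confirmed or not confirmed for a claimed disease. A page selected because it shows the claimed disease says nothing reliable about the others.

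If the non-claimers' status is missing, the analyst can either restrict the table to claimers or fill the empty row with assumed negatives. The first makes kappa uninformative. The second raises both kappa and percent agreement using data that nobody collected. At stake is the published statement on how far self-reported diagnoses can be trusted, which could depend on a coding convention.

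**Working it through.** **Inputs.** Only the cohort size, 1500, and the seven categories come from the document. It states no kappa, precision target or expected confirmation rate, so there is no figure to reproduce. The following are assumptions for illustration: 300 people claim rheumatoid arthritis (RA); 240 of these claims are confirmed; between 0% and 10% of the 1200 non-claimers have RA in their record.

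**Formula.** Let *a* = claimed and confirmed, *b* = claimed and not confirmed, *c* = not claimed but in the record, *d* = neither, with *n* their sum. Then Po = (*a* + *d*)/*n*; Pe = [(*a* + *b*)(*a* + *c*) + (*c* + *d*)(*b* + *d*)]/*n*²; kappa = (Po − Pe)/(1 − Pe).

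**Step 1: claimers only (*c* = *d* = 0).** Po = 240/300 = 0.80. Self-report is always yes, so Pe = 1 × 0.80 = 0.80 and kappa = 0/0.20 = 0. With 285 of 300 confirmed, Po = Pe = 0.95 and kappa is again 0. With 300 of 300, Po = Pe = 1 and kappa is 0/0, undefined. Percent agreement in this table is the confirmed proportion, that is, the positive predictive value (PPV).

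**Step 2: all 1500, unclaimed coded as negative (*c* = 0).** Po = (240 + 1200)/1500 = 0.960. Pe = 0.20 × 0.16 + 0.80 × 0.84 = 0.704. Kappa = 0.256/0.296 = 0.865.

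**Step 3: the same cohort if the non-claimers' record status were known.**

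| Non-claimers with RA | *c* | Po | Pe | kappa |
|---|---|---|---|---|
| 0% | 0 | 0.960 | 0.7040 | 0.865 |
| 2% | 24 | 0.944 | 0.6944 | 0.817 |
| 5% | 60 | 0.920 | 0.6800 | 0.750 |
| 10% | 120 | 0.880 | 0.6560 | 0.651 |

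The coding in Step 2 reports 0.865 in every row. In 200,000 random 2×2 tables, moving *c* into *d* never lowered kappa, so any error is in the favourable direction.

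**Step 4: sensitivity to how common the claim is.** With a PPV of 0.90 and 10% claiming, the coded kappa is 0.942, against 0.850, 0.736 and 0.590 at 2%, 5% and 10% unreported. With 50% claiming it is 0.900, against 0.880, 0.850 and 0.800. For a given share of unreported disease, the inflation is larger for the less often claimed disease.

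**Step 5: pooling over categories.** Assume 1.5 claims per person: 1500 × 7 = 10,500 person-by-disease cells, 2250 of them claims. If only half the claims are confirmed, Po = (1125 + 8250)/10,500 = 0.893, Pe = 0.724 and kappa = 0.61. The assumed negatives dominate the table.

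**Step 6: what the claims do support.** For 240 of 300 confirmed, the PPV is 0.80. The Wilson interval has centre (0.80 + 3.84/600)/(1 + 3.84/300) = 0.796 and half-width 1.96 × √(0.16/300 + 3.84/360,000)/(1 + 3.84/300) = 0.045, giving 0.751 to 0.841. No assumption about non-claimers is needed.

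**The case against.** Five points can be made for the plan.

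1. **The physician form may list every disease.** This stands. A reader might infer that the status of unclaimed diseases is never obtained for anyone. The article does not support that: the template is not shown, and its content is the kind of detail a condensed article leaves out. The problem is established only for the record-upload route.
2. **Kappa need not be built disease by disease.** This stands in part. A reader might infer that kappa must be either zero or inflated. A single kappa of claimed category against verified category, with a not-confirmed level, is neither. Assuming one diagnosis each and claims split 700/300/200/100/80/60/60, the squared shares sum to S = 0.286, and kappa = PPV(1 − S)/(1 − PPV × S). That gives 0.42, 0.74 and 0.87 at PPV 0.50, 0.80 and 0.90. But it depends only on the PPV and the mix of claims, so it adds little beyond the PPV. It also assumes one label per person, while the study allows several.
3. **Percent agreement is already planned.** This stands. Among claims it is the PPV, so the valid summary sits next to kappa in the same sentence. It loses that meaning if assumed negatives enter: in the RA example it rises from 0.80 to 0.96.
4. **The inflation rests on assumed prevalence.** This stands. Participants are asked to report all their diagnoses, so unreported disease may be rare. At 0.5%, 1% and 2%, kappa would be 0.85, 0.84 and 0.82, against 0.86; at 0% nothing is lost. But record-route data cannot show where in that range the study lies.
5. **A separate analysis plan may settle the table.** It can choose a table. It cannot supply reference data that were not collected.

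**Conclusion.** The concern holds in a limited form. For participants verified by an uploaded record page, a per-disease kappa cannot measure the validity of self-report: it is 0 or undefined among claimers, and with unclaimed diseases coded as verified negatives it is biased upward by an unknown amount. In the RA illustration that amount is nil at 0% unreported disease, about 0.05 at 2%, 0.11 at 5% and 0.21 at 10%. These sizes rest on assumed counts.

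It does not follow that kappa is meaningless for the whole cohort, or that the validation aim fails. If the physician form asks about every listed disease, kappa is estimable on that route, and the PPV is estimable on both. This should be fixed because it concerns a stated aim and the change is small; a valid summary is already within the plan's reach.

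**What to change.** - In the Analysis plan, make the validity measure the proportion of claimed diagnoses confirmed, by disease, with a 95% confidence interval, and say that this is percent agreement among claims.
- Report kappa, sensitivity and specificity by disease only in participants whose provider form records yes or no for every listed disease. If the form is not already such a checklist, make it one.
- State that unclaimed diseases are not counted as verified negatives on the record-upload route.

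The cost is a change of wording and, if needed, a revised form. The checklist has to be in place while forms are still being collected, because missing reference status cannot be recovered in analysis. The downside is that kappa will be available only in the physician-form subset. Participants choose their route, so that subset is self-selected, and the report should state this as a limitation.

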## Data management and Confidentiality

All data will be collected and stored in the REDCap data management system provided by the University of Delaware Center for Human Research Coordination (CHRC). These systems are password protected and require two-factor authentication to access all data.

## Ethics

This observational study received institutional review board approval from the University of Delaware. All participants must provide written informed consent and sign the Health Insurance Portability and Accountability Act (HIPAA) release form before participation. Participants have the right to withdraw at any time without penalty.

## Discussion

The OASIS study is a novel observational study of a completely online cohort of adults with rheumatic diseases. This study aims to determine reliability of patient reported diagnoses for rheumatic diseases and address the current gap in literature regarding the relationship of physical activity, pain, and function in adults with less common rheumatic diseases. Previous studies have examined the relationship between physical activity, pain, and function in individuals with OA^13,19–21^ and RA^15,22–25^, however little research on these relationships exists for lupus, psoriatic arthritis, and other rheumatic diseases which limits the ability to provide tailored activity recommendations.

### Strengths

OASIS utilizes a novel completely online recruitment strategy. This allows for recruitment of a geographically diverse sample and inclusion of individuals from rural areas, which are typically understudied. Additionally, this is the first study to include individuals with all rheumatic diseases, allowing for comparisons across rheumatic diagnoses which were not previously possible. The use of validated outcome measures strengthens the reliability of the data, and inclusion of physician verification of diagnoses increases accuracy of rheumatic disease classification.

### Limitations

Since all outcomes will be self-report questionnaires, there is a risk of recall and/or social desirability bias. OASIS is also a cross-sectional study which limits the ability to determine causal relationships between outcomes. Additionally, the online recruitment strategy may risk excluding those less likely to have access to the internet. However, data from the Pew research center shows that in 2024 96% of adults in the US report using the internet.^43^

### Implications

Results from OASIS will inform methods to conduct internet-based recruitment for future studies. Additionally, data could potentially be used to identify differences in clinical presentation and disease specific needs for treatment across rheumatic diseases. Results could also inform tailored exercise recommendations for understudied rheumatic diseases.
